#### Outcomes

The clinic-level primary outcomes for this study include clinic staff attitudes and environment, observed discrimination, and stigmatizing avoidance behaviors toward AGYW, as measured by staff surveys and the clinic audits. The AGYW-level primary outcomes include the level of PrEP readiness, uptake, and adherence (as measured by self-report and DBS), and SRH uptake. The AGYW-level secondary outcomes include frequency of substance use, as measured by the RRBA and biological drug screening and breathalyzer tests to assess recent alcohol use; GBV, assessed through self-reported experiences of emotional, physical and sexual abuse; sexual risk as measured by condomless sex, impaired sex, other sex partners; self-reported frequency of experienced stigma.

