### Data collection: adolescent girls and young women level

#### Recruitment

AGYW are recruited in communities that are in the study clinic’s catchment area. Recruitment is conducted through research study staff, who may also be assisted by trained WBOTs associated with the study clinics. However, screening is only conducted and performed by research study staff. Recruitment is conducted via street outreach at identified areas where AGYW are known to frequent. Street outreach is an established recruitment method that has been used successfully in previous research studies [50–53], including Tshwane WHC studies to reach and recruit a high number of women most at risk of HIV. Study staff visit these hotspots regularly to establish a known presence in the community and gain rapport with community members. Recruitment also is conducted through referrals from the clinic or other staff who conduct HIV and/or pregnancy testing in the community, such as HIV and AIDS, STI, and TB (HAST) counselors.

Participant eligibility criteria include the following: (1) identify as female; (2) HIV negative status; (3) between ages 16 and 24 years; (4) have had condomless sex in the past 3 months with a male partner; (5) not currently pregnant and do not want to get pregnant within the next year; (6) interested in taking a daily pill to prevent HIV (PrEP); (7) not having previously participated in the formative phase of the study; (8) not previously or not currently participating in any other PrEP-related project or research study; (9) not previously or not currently participating in any other HIV study in Tshwane; (10) not on multidrug-resistant tuberculosis (MDR-TB) treatment; (11) lives in one of the target communities; (12) intends to stay in the Tshwane district for the next 12 months; (13) agrees to provide contact information; (14) willing to undergo rapid HIV testing; and (15) willing to undergo pregnancy testing.

Because of the eligibility requirement of an HIV-negative and nonpregnant status, interested potential participants must first consent to rapid testing for HIV and pregnancy to confirm eligibility. Additionally, co-enrollment in another HIV study is also checked and any individual who is currently enrolled is excluded.

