#### Intake assessment

After consenting/assenting, participants also sign a release of medical records permitting the release of information on their SRH, PrEP screening and monitoring results, and other referrals and care pertinent to the study.

Participants take a breathalyzer test to detect recent alcohol use (conducted earlier in the appointment because of the limited detection window for alcohol breath scans) and provide urine for drug screening, locator information is collected, and a photograph of the participant is taken to identify the participant for subsequent appointments. This photo is returned or shredded at the final appointment. The participant then completes a baseline questionnaire on a computer tablet via audio computer-assisted self-interview (ACASI) in either English or Setswana (see AGYW Health CoOp Questionnaire in Supplementary File 3). Trained field staff are available to assist the participant at any time and provide referrals based on prompts related to self-reported violence, symptoms of psychological distress, or suicidal ideation experienced in the past 3 months that are triggered as the participant completes the questionnaire. The questionnaire is derived from components of the youth-specific modification of the Revised Risk Behavior Assessment (RRBA) [54], which has been adapted and modified for many studies in South Africa. The modified RRBA for this study contains sections on PrEP knowledge, contraception and other SRH services access and utilization, sexual communication, STI symptoms, alcohol and other drug use, relationship equity and sexual control, economic dependence, personal agency, psychological distress, victimization, and peers and social support. After completing the questionnaire, urine drug screening results are provided to assess the recent use of amphetamine, methamphetamine, benzodiazepine, cocaine, marijuana, opioids, and MDMA. These screening tests are repeated at 3-, 6-, and 9-month follow-up assessments.

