#### Sexual and reproductive health services

All participants who complete their baseline appointment are actively referred to the designated youth-friendly nurse or youth-friendly service at their respective study clinic for SRH services; specifically, birth control services. Follow-up on these linkages is conducted at the 3-month follow-up appointment for participants in the control groups and during monthly check-ins for participants in the YWHC groups.

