#### Analysis

Analysis of primary outcome measures will determine whether the provision of S&D reduction training for clinic staff and the YWHC intervention for AGYW will increase PrEP readiness, PrEP uptake, and PrEP adherence, and SRH uptake.

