#### AGYW level

The testing of Aim 3 will be done by intention to treat analysis, examining the effects of intervention groups at both levels (clinic and individual) on PrEP readiness, uptake and adherence. PrEP uptake will be defined as any use of PrEP. We will consider both short-term uptake within the first 3 months after study enrollment and uptake at any point during the 9-month follow-up period. Initially, we will calculate the proportion of AGYW with any use of PrEP, overall, and within each study arm, calculating 95% confidence intervals using the binomial distribution. Given the need to consider the influence of the cluster randomization by clinic, we will use generalized estimating equations (GEE) [61] models with a logit link and an exchangeable correlation structure to estimate the effects of randomization groups on both short-term (3-month follow-up) and long-term follow-up period (9-month follow-up). Models will include both intervention groups (i.e., S&D reduction training and YWHC) as covariates. Effects of clustering by randomization clinic may be examined by adjusting the variance by the inflation factor [1 + (m-1)r], where *m* is the average clinic size and *r* is the interclass correlation estimate. If the Hausman assumption of correlation between the random and fixed effects is violated, then we may include fixed effects representing cluster identification.

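### SRH uptake: baseline contraception and SRH use should be a pre-specified covariate, not one admitted only when arms look different

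*Protocol article*

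**What the plan says.** All references are to the protocol article.

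- **Outcomes** lists the primary endpoints at participant level: "The AGYW-level primary outcomes include the level of PrEP readiness, uptake, and adherence (as measured by self-report and DBS), and SRH uptake". **Analysis** asks whether the two interventions "will increase PrEP readiness, PrEP uptake, and PrEP adherence, and SRH uptake".
- **Recruitment** gives 15 eligibility criteria. Two bear on contraception: "not currently pregnant and do not want to get pregnant within the next year" and "have had condomless sex in the past 3 months with a male partner". Neither excludes a woman using a non-condom method, and no other criterion concerns current contraception.
- **Sexual and reproductive health services** makes no distinction between users and non-users: "All participants who complete their baseline appointment are actively referred to the designated youth-friendly nurse". That section names birth control as the service meant by the referral.
- **Intake assessment** lists among the sections of the baseline questionnaire "contraception and other SRH services access and utilization".
- **AGYW level** defines PrEP uptake as any use but gives no matching definition for SRH uptake. On the models it says: "Models will include both intervention groups (i.e., S&D reduction training and YWHC) as covariates". Further baseline covariates (sociodemographic factors and behavioural risks) are to be added if descriptive analyses suggest that they differ between arms. The hypotheses in the same section speak of SRH utilization rather than uptake.

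**The concern.** Women who want to avoid pregnancy for a year may well include some who already use birth control. For them, being a user at follow-up is mostly a matter of continuing, so baseline use is likely to be one of the strongest predictors of the outcome. The stated rule for covariates does not respond to that. It is triggered by differences between arms, whereas the gain from adjusting for a strong predictor exists when arms are perfectly balanced. Under the rule, the better the balance, the more likely the covariate is left out.

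If continuing use counts, two things follow. The difference in all women is smaller than the difference among women who could newly start. The mixture of users and non-users also adds outcome variance that adjustment would remove. At stake is the power of a primary comparison that is also a named hypothesis for the S&D training. A smaller problem is that a covariate chosen after looking at the arms makes the primary model depend on the data.

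**Working it through.** **Inputs from the article** (Sample size and power; Randomization): two-sided 0.05, power 0.80, ICC 0.01, 12 clinics, 75 women per clinic, 10% attrition, 1:1:1:1 allocation. Each main effect therefore compares 6 with 6 clinics.

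**Assumed, because the article gives no figure:** share of prior users q = 10%, 30%, 50%; 90% of prior users still using at follow-up in both arms; uptake among non-users of 30% (control) and 48% (intervention), an 18-point effect. Continuing use is counted as uptake.

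**Step 1, effective sample size.** m = 75 × 0.9 = 67.5. Design effect = 1 + 66.5 × 0.01 = 1.665. Effective n per level = 6 × 67.5 / 1.665 = 243.

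**Step 2, the plan's own figure.** Solving the two-proportion test for 80% power with n = 243 gives detectable differences of 8.9 points at a 10% control rate, 11.0 at 20%, 12.2 at 30%, and 12.6 at 40% and 50%. The stated 9 to 13% is reproduced for the main-effect contrast.

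**Step 3, rates in all women.** Control: p0 = 0.9q + 0.30(1−q). Intervention: p1 = 0.9q + 0.48(1−q). Difference = 0.18(1−q).

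**Step 4, variance.** Unadjusted, the sum over arms is p0(1−p0) + p1(1−p1). Adjusted for baseline use, only the variance within users and within non-users remains: control q(0.09) + (1−q)(0.21), intervention q(0.09) + (1−q)(0.2496). SE = √(sum/243). Power = Φ(difference/SE − 1.96). The design effect is held at 1.665 throughout.

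| q | p0, p1 | Difference | Variance sum, unadjusted → adjusted | SE, unadjusted → adjusted | Power, unadjusted → adjusted |
|---|---|---|---|---|---|
| 10% | 0.360, 0.522 | 0.162 | 0.480 → 0.432 | 0.0444 → 0.0421 | 95% → 97% |
| 30% | 0.480, 0.606 | 0.126 | 0.488 → 0.376 | 0.0448 → 0.0393 | 80% → 89% |
| 50% | 0.600, 0.690 | 0.090 | 0.454 → 0.320 | 0.0432 → 0.0363 | 55% → 70% |

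With only 12 clinics the normal approximation flatters every figure. A noncentral t on 9 df (12 clinics less three parameters), with difference/SE as noncentrality, gives 90% → 93%, 71% → 81% and 46% → 60%. The levels fall and the gain remains.

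**Step 5, should the primary analysis be restricted to non-users instead?** At q = 50%, m = 33.75, the design effect is 1.3275 and n = 6 × 33.75 / 1.3275 = 153. SE = √(0.4596/153) = 0.055 and power is 91%, against 55% in all women without adjustment. That advantage rests on equal continuation in the two arms. If the intervention also moves continuation from 80% to 90%, then p0 = 0.55, p1 = 0.69 and the difference is 0.14. Power in all women is then 90% unadjusted and 96% adjusted, against 91% in non-users. At q = 60% under the same assumption it is 88% (all women, unadjusted) against 85% (non-users). Restriction may help or hurt; adjustment helped in every scenario run.

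**The case against.** A reader might infer that continuing users are counted as uptake, and that the primary analysis should therefore be moved to baseline non-users. The article does not support this.

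- It never says how SRH uptake is counted. It could be a new start, a linkage visit, a service contact or current use. If it is a new start or a new contact, continuing users are not counted. An operational definition may properly sit in the full protocol or analysis plan, so its absence here is not the finding.
- The intention-to-treat sentence names only the PrEP outcomes. The birth-control wording describes the referral, not the endpoint.
- All women are referred, so a current user can also link to the clinic. The hypothesis is about utilization, and the Background names stigma as a barrier to retention as well as reach. Keeping users in care is a plausible effect of the S&D training, and all women are a legitimate target population.
- Randomization means that prior users do not bias the comparison in expectation, although chance imbalance is possible with 12 clusters.
- The article does not say that baseline SRH data go unused. Covariates may enter conditionally, and exploratory moderation analyses are planned.

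All of this stands against making initiation in non-users the primary outcome. It does not answer the narrower point: the covariate rule that the article does state depends on imbalance, and imbalance is the wrong test for a strong predictor.

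**Conclusion.** The point holds as a matter of precision, not validity. SRH uptake is primary, current users may enrol, their status is recorded at baseline, and the stated rule may leave that status out of the model when arms look similar. If continuing use counts, adjustment is worth about 2 points of power with 10% prior users, 9 with 30% and 15 with 50%. These figures rest on assumed 90% continuation, 30% control uptake, an 18-point effect in non-users, the article's ICC of 0.01 and a normal approximation. If few women are prior users, or if uptake means a new service contact that baseline use hardly predicts, the gain is small. The documents do not establish that the primary analysis is wrong, that its result would be biased, or that restriction to non-users would be better.

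**What to change.** 1. For SRH uptake, replace the imbalance trigger with pre-specified adjustment for baseline contraception and SRH use in the all-women analysis.
2. Pre-specify two supportive analyses: initiation among baseline non-users, and continuation among baseline users. Together they show where an overall effect comes from.
3. State in the outcome definition whether continuing use counts, and use one term throughout, uptake or utilization.
4. Because the models use a logit link, adjusting for a strong predictor changes what the odds ratio means. Report a standardized risk difference beside it.

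The cost is wording in the analysis plan: the variable is already in the baseline questionnaire, and no extra women or visits are needed. The change should be fixed before outcome data by arm are seen. One check is needed. The questionnaire comes before the YWHC workshops, but the article does not set out how participants' enrolment is timed against the clinic training. For the S&D contrast, confirm that baseline use was recorded before the training could have affected it.

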#### Sample size and power

For the AGYW analyses, the total sample size and number of clusters (clinic catchment areas) were selected to ensure sufficient power to detect meaningful differences in our primary outcomes, while also balancing considerations tied to reducing possible contamination (exposure to the intervention in control clusters) and implementation feasibility with a set number of clinics in the study area. Sample size estimates for tests of two proportions in a cluster-randomized design [56] were conducted for a 2-sided test with significance level of 0.05, power of .80, and intra-cluster correlation of 0.01 (based on our team’s past research in Cape Town communities), assuming 10% attrition over the 9-month follow-up period [52, 57]. This was not adjusted for multiple comparisons. Based on these parameters and calculations, the study sample includes 12 clusters (defined as clinics and their catchment areas), with a total sample size of 900 AGYW enrolled, 75 per cluster (clinic catchment area). This sample was chosen to ensure that meaningful differences in the primary outcomes of PrEP readiness, uptake, and adherence between groups would be detectable. We are powered to detect a difference between 9 to 13% in primary outcomes. Power analyses were first conducted in PASS software [58] and were refined in Stata [59] (see PrEPARE Additional Power Calculation Information in Supplementary File 4).

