#### Follow-up assessments

Participants in both study arms return for their 3-, 6- and 9-month behavioral and biological follow-up assessments. Research staff track participants using locator information provided during the intake appointment to help retain participants. The follow-up visit includes reconsenting; updating locator information; a follow-up questionnaire via ACASI; and biological testing for HIV, pregnancy, alcohol use (breathalyzer), and other recent drug use. Dried blood spots (DBS) also are collected at these appointments from participants who report to be on PrEP. The PrEP medication used for this study is a combination of FTC 200 mg/TDF 300 mg tablets. The DBS are used to assess the presence of tenofovir diphosphate (TFV-DP), a measure of cumulative and recent adherence, using a previously validated methodology [55].

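### The 9 to 13 point detectable difference matches a normal approximation at control rates of about 10–50%; with 12 clinics and a test that holds the 5% level, power there is about 69–74%, not 80%

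*Protocol article*

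**What the plan says.** The Sample size and power section of the protocol article describes "Sample size estimates for tests of two proportions in a cluster-randomized design", for a "2-sided test with significance level of 0.05, power of .80, and intra-cluster correlation of 0.01", "assuming 10% attrition over the 9-month follow-up period". It arrives at 12 clinics, "with a total sample size of 900 AGYW enrolled, 75 per cluster", and concludes: "We are powered to detect a difference between 9 to 13% in primary outcomes". It names PrEP readiness, uptake and adherence as the outcomes concerned. It does not give the control-group rates, and it does not say whether a normal or a t reference was used. For further detail it points to Supplementary File 4, which is not among the documents at hand.

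The Randomization section puts the 12 clinics in three strata of four and allocates them 1:1:1:1 within each stratum. Each factor is therefore a comparison of 6 clinics with 6. The AGYW-level Analysis section plans logit GEE with an exchangeable correlation, with both factors in the model.

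**The concern.** The clinic is the randomised unit, so the between-clinic variance is estimated from 12 clinics. After the model terms are fitted, that leaves 10 degrees of freedom or fewer. A sample size formula that uses 1.96 and 0.84 treats this variance as known. If the printed range was obtained that way, the 5% level and the 80% power cannot both hold. Either the test uses a small-sample reference and loses power, or it keeps the normal cut-off and rejects a true null too often. A null result might then be read as excluding a 9 to 13 point effect with a 20% chance of a miss, when that chance is closer to 30%.

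**Working it through.** **Inputs from the protocol article.** 75 women per clinic, 10% attrition, ICC 0.01, two-sided 0.05, power 0.80 (Sample size and power); 6 versus 6 clinics per factor, three strata (Randomization); both factors in the model (Analysis, AGYW level). **Assumed:** the control rate p0, taken over 10–50% for the main range because the article does not give it.

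**Effective sample size.** Retained per clinic: 75 × 0.9 = 67.5. Design effect: 1 + (67.5 − 1) × 0.01 = 1.665. Per side: 6 × 67.5 = 405 women, so the effective n is 405 / 1.665 = 243.2.

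**Standard error.** SE = √{[p0(1 − p0) + p1(1 − p1)] / 243.2}.

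**Reproducing the printed range.** Under the normal approximation, the detectable difference solves d / SE = 1.960 + 0.842 = 2.802:

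- p0 = 10%: 8.9 points
- p0 = 20%: 11.0 points
- p0 = 40–45%: 12.6 points, the maximum over p0 (12.7 with a pooled variance)

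Rounded, this is 9 to 13. A comparison of single cells, 3 versus 3 clinics, gives 13.3 to 17.6 points over 10–50%, so the statement fits the factorial main effects and not the four-cell contrasts.

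**Same differences with a t reference.** Residual df are 10 (plain 6 versus 6), 9 (both factors), 8 (one factor plus strata) or 7 (both factors plus strata). Power = P(T > t(0.975, df)), with T noncentral t and noncentrality d / SE.

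| | Normal | 10 df | 9 df | 8 df | 7 df |
|---|---|---|---|---|---|
| Power at the unrounded normal-based difference | 80% | 71% | 70% | 69% | 67% |
| Power, 10% vs 19% (SE 0.0317, d/SE 2.84) | 81% | 73% | 72% | 70% | 69% |
| Power, 40% vs 53% (SE 0.0448, d/SE 2.90) | 83% | 74% | 73% | 72% | 70% |
| 80%-power difference, p0 = 10% (points) | 8.9 | 10.0 | 10.1 | 10.3 | 10.6 |
| 80%-power difference, largest over p0 = 10–50% (points) | 12.6 | 14.0 | 14.1 | 14.4 | 14.7 |

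**Cross-check by simulation.** Beta-binomial data, 6 versus 6 clinics, 20,000 runs per setting, t-test on clinic proportions (10 df): power is 71.5–72.7% at the normal-based differences, and the type I error is about 5%.

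**Keeping the normal cut-off.** In the same simulation, using 1.96 with the estimated between-clinic variance keeps power at about 79–80% but rejects a true null in 7.6–8.2% of runs. Analytically, 2 × P(T > 1.96) is 7.8% at 10 df and 9.1% at 7 df.

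**Could a t-based calculation have produced 9 to 13?** Yes, at other control rates. With 10 df, 9 points has 80% power at p0 of about 7%, and 13 points at p0 of about 25%. With 7 df, the corresponding rates are about 6% and 20%.

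**The case against.** The strongest reply is that the control rates and the reference distribution may be in Supplementary File 4. If the planners worked with control rates of about 7–25%, a t-based calculation gives the printed range. At a 5% control rate, 9 points has 84–87% power with t; at 20%, 13 points has 80–84%. This stands. A reader might infer that the range can come only from a normal approximation, or that the trial is underpowered on its own assumptions. The article does not support either inference, because it does not state those assumptions.

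The degrees of freedom also depend on the final model. The article lists both factors but not the strata, so 7 df is one possibility and not the plan's stated model. A small-sample correction to GEE is commonly left to the analysis plan, so its absence from the article is not itself an error.

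Two further readings are tempting and should not be pressed.

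- **Adherence.** Dried blood spots are collected "from participants who report to be on PrEP", so a reader might infer that the power claim fails outright for adherence. But Aim 3 is analysed by intention to treat, and women not on PrEP can be counted as non-adherent without an assay, which keeps the full denominator. A larger detectable difference follows only if adherence is analysed among users, and its size depends on a user proportion that the article does not give.
- **ICC.** A reader might infer that "intra-cluster correlation of 0.01" is too low because PrEP is delivered through the clinics. The article states the value and says it comes from the team's own community research in Cape Town. It gives no figure that supports a larger one.

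It is also fair to say that the gap is modest, about 1 to 2 points in detectable difference, and that a null result should be read from its confidence interval.

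**Conclusion.** The concern holds in a limited form. For control rates of about 10–50%, the printed 9 to 13 points is what a normal approximation gives for the two main effects. With 12 clinics and a test that holds the 5% level, power at 9 points (control rate 10%) or 13 points (40%) is about 69–74%; at the unrounded normal-based differences it is 67–71%. Differences with 80% power run from about 10 to 14 points with 9–10 df, or from 10.6 to 14.7 with 7 df.

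This rests on three things: the assumed control rates, an ICC of 0.01 as stated, and a t reference on clinic-level degrees of freedom. If Supplementary File 4 shows control rates of about 7–25% and a t-based calculation, the printed range stands for those rates, and all that is needed is to say so.

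**What to change.** Recompute the detectable difference with cluster-based degrees of freedom, and print the control rates and the df beside it. Subject to the true control rates, the statement could read: *For each factor's main effect among all enrolled AGYW, the trial has 80% power for differences of about 10–15 points (control rates 10–50%, ICC 0.01, t reference with 7–10 df).* Fix the final df once it is decided whether strata enter the model, and use the same small-sample reference for the GEE test so that the stated level and power refer to the same procedure.

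Give a separate adherence figure only if adherence will be analysed among PrEP users. A table over larger ICCs is an optional sensitivity display.

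The cost is a less favourable printed figure and a short recalculation. No clinics or participants are added.
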